## Abstract

**Background:**

Major depressive disorder (MDD) is a common, chronic, debilitating mood disorder that causes serious functional impairment and significantly decreased quality of life. Pharmacotherapy represents the first-line treatment option; however, only approximately one third of patients respond to the first treatment because of the ineffectiveness or side effects of antidepressants. Precision medicine in psychiatry might offer clinicians the possibility to tailor treatment according to the best possible evidence of efficacy and tolerability for each subject. In this context, our study aims to carry out a clinical validation of a combinatorial pharmacogenomics (PGx) test in an Italian MDD patient cohort with advocacy license independence.

**Methods:**

Our study is a prospective participant- and rater-blinded, randomized, controlled clinical observational trial enrolling 300 MDD patients who are referred to psychiatric services to receive a new antidepressant due to the failure of their current treatment and/or the onset of adverse effects. Eligible participants are randomized to the TGTG group (Treated with Genetic Test Guide) or TAU group (Treated as Usual). For all subjects, DNA is collected with a buccal brush. The primary outcome is the reduction in depressive symptomatology. The secondary outcomes involve a range of scales that assess MDD symptoms and social functioning outcomes. The assessment is performed at four timepoints: baseline and 4, 8, and 12 weeks.

**Discussion:**

This project represents the first randomized controlled clinical trial to investigate whether a non-commercial PGx test improves outcomes in an MDD naturalistic cohort. Moreover, the identification of new genetic variants associated with non-response or side effects will improve the efficacy of the test, leading to further cost-saving.

**Trial registration number:**

ClinicalTrials.gov NCT04615234. Registered on November 4, 2020.

**Supplementary Information:**

The online version contains supplementary material available at 10.1186/s13063-021-05775-8.

## Background

Major depressive disorder (MDD) is the most common psychiatric disease worldwide and represents a leading cause of years lived with disability, resulting in a substantial socio-economic impact [1]. The main goal of treating MDD is to achieve remission and to maintain the therapeutic effects over time. Despite the availability of different classes of antidepressant drugs (ADs), the success of pharmacological treatment is still unsatisfactory, and matching a patient to his/her optimal treatment generally requires multiple trials of different treatments, with the sobering observation that the more treatments that are tried without success, the less likely a successful outcome is. Only approximately one third of patients achieve remission after the first treatment course, while another approximately one third develop treatment-resistant depression (TRD) [2, 3]. The high percentage of treatment failure or incomplete remission could be a consequence of intrinsic biological and environmental heterogeneity among MDD patients [4, 5], suggesting that biomarkers of the response to ADs would be useful for clinicians to guide treatment at the individual level. In this context, pharmacogenomics (PGx) testing has the potential to reduce antidepressant discontinuation due to side effects and increase efficacy.

Recently, assay-guided treatment has shown promising results. Several observational and randomized controlled trials (RCTs) have been conducted to investigate the impact of pharmacogenetics or pharmacogenomics testing on antidepressant outcome in MDD patients with interesting results [6, 7].

This article presents the protocol for the RCT and is written to comply with the recommended SPIRIT guidelines for RCT protocols (Additional file 1).

### Aim of the study

The study was designed as an observational, prospective participant- and rater-blinded randomized, controlled trial (shown in Figs. 1 and 2) to evaluate the clinical efficacy of a combinatorial PGx test to guide clinician’ treatment decision-making in a naturalistic setting. This study will be conducted in an Italian MDD patient cohort with advocacy license independence. In particular, the main objective of the study is to assess the role of a PGx test in improving the response rate and leading to a greater amelioration of depressive symptoms in MDD patients. The secondary objective is to evaluate the use of PGx in decreasing the side effects of antidepressants. Moreover, the study aims to provide data about the use of the PGx test in decreasing depressive-related symptomatology (such as anxiety symptoms and functionality) and the possible influence of vulnerability factors, such as early and recent stressful events, on the main outcomes.

**Fig. 1 Fig1:**
[figure not shown]
Flowchart of the trial design

**Fig. 2 Fig2:**
[figure not shown]
Schedule of enrolment, interventions, assessments, and outcomes of the PANDORA trial

## Methods

### Eligibility criteria

Three hundred MDD out-patients are voluntarily enrolling in the study. Patients are referred to psychiatric services (University Department of Mental Health, Spedali Civili Hospital, and IRCCS Istituto Centro San Giovanni di Dio Fatebenefratelli – Brescia, Italy) to receive a new AD due to the failure of their current treatment and/or the onset of adverse effects. The diagnostic inclusion criteria are as follows: a current diagnosis of unipolar depression according to the Diagnostic and Statistical Manual of Mental Disorders-5 (DSM-5) [8] classification system criteria with a Hamilton Depression Rating Scale (HAMD-17) [9] score ≥14, age range 18–65 years, and Caucasian ethnicity. The exclusion criteria are cognitive impairment (Mini Mental State Examination MMSE <24) [10]; neurological disorders; diagnosis of MDD with psychotic features, bipolar I and II disorders, schizophrenia spectrum and other psychotic disorders, obsessive-compulsive disorder, post-traumatic stress disorder, alcohol and substance abuse in the last 3 months; comorbidity with personality disorders (cluster A and/or B); pregnancy; and comorbidity with other severe medical illness. Diagnoses are confirmed using the Italian version of the Structural Clinical Interview for DSM-5 disorders (SCID-5-CV) [11] and the Structural Clinical Interview for personality disorders (SCID-5-PD) [12]. After the enrolment of MDD patients in accordance with the inclusion and exclusion criteria and after obtaining written informed consent, for all patients, DNA is collected through a buccal brush.

### Randomization and concealment

Eligible patients are randomized to the Treated with Genetic Test Guide (TGTG) group or Treated as Usual (TAU) group. The allocation to the TGTG or TAU group is performed with simple randomization software (http://glimmpse.samplesizeshop.org/) by the project manager who is not involved in either the evaluation or the treatment. The allocation of the patients is communicated directly from the project manager (AM) to the prescriber. None of the other people involved in the projects are informed and/or have access to the allocation information. The randomized allocation sequence of the trial participants is conserved in a double file protected by a double password owned by the PI (MG) and the project manager (AM).

### Assessments

The clinical assessment is carried out at 4 timepoints: baseline (T0), after 4 (T4), 8 (T8), and 12 (T12) weeks of AD treatment. The evaluations are performed using the HAMD-17, the Beck Depression Inventory II (BDI-II) [13]; the Beck Anxiety Inventory (BAI) [14], to evaluate the clinical efficacy of the therapy; the MINI-ICF-APP [15] to monitor changes in psychosocial functioning; and the UKU (Udvalg for Kliniske Undersogelser) Side Effects Rating Scale [16] to observe the adverse events. Moreover, the Childhood Experience of Care and Abuse Questionnaire (CECA.Q) [17] and the Paykel’s Recent Life Events Scale [18] are assessed only at T0.

### Blinding

All the participants are evaluated by assessors who are not otherwise involved, pharmacological treatment, or patient allocation. The treating physicians are unblinded. Neither the assessors nor prescribers are involved in the data analysis.

### Pharmacogenetic report and intervention procedure

The clinicians of the patients in the TGTG group receive the PGx test report within 48 h, and all the participants start their new treatment within 72 h. The PGx test results for the subjects in the TAU are provided to the prescriber once all week 12 visit procedures are completed. AD monotherapy is mandatory, with the exception of the association of benzodiazepines and/or hypnotics when necessary. If the patients need another change in antidepressant monotherapy, they stay in the study protocol, and the changes are annotated. If the patients need a combination and/or augmentation treatment with antipsychotics and/or mood stabilizers, they are excluded from the study.

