### Statistical analysis

Analysis of variance (ANOVA) or the Kruskal–Wallis and Mann–Whitney *U* nonparametric tests and the chi-squared test will be used to analyze differences in continuous and categorical variables, respectively, between groups. Pearson’s correlation analysis will be used to evaluate bivariate correlations. Parametric and nonparametric tests will be used to meet relative assumptions (i.e., distribution, sample size).

To pursue our primary outcome, the analyses will be performed for patients who complete the study through week 8. The analysis will be performed using mixed-effects models with repeated measures (MMRM) to examine the effect of time and group (TGTG vs. TAU) on the reduction in the HAMD-17 score. The model includes the fixed effect continuous factor baseline HAMD-17 and fixed effect categorical factors, which are the treatment group (TGTG and TAU; 2 levels), visit (weeks 4 and 8; 2 levels), and treatment x visit interaction. The mean changes in the HAMD-17 at week 8 in the TGTG and TAU groups will be estimated and tested utilizing the LS means from the treatment x visit interaction in the MMRM model. The primary analysis will test the difference (contrast) between the week 8 least squares (LS) means at a two-sided significance of 0.05. To achieve the secondary outcome, the generalized linear mixed model will be used for response and remission analyses. The analyses of the tertiary outcomes will be performed for exploratory purposes with the same statistical models. Comparisons between the TGTG and TAU means at all timepoints of evaluation will also be performed for descriptive purposes. Finally, an intention-to-treat (ITT) analysis will be performed for all the patients who undergo at least one post-treatment assessment for efficacy during the study. The last observation will be carried forward on the HAMD-17. All the statistical analyses will be performed using R Statistical Software (R Foundation for Statistical Computing, Vienna, Austria).

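### Patients removed for combination or augmentation before week 8 drop out of the primary estimate, and their place in the intention-to-treat set is not settled

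*Protocol article*

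**What the plan says.** In the protocol article, the section Pharmacogenetic report and intervention procedure makes antidepressant monotherapy mandatory and treats two later events differently. For a further switch: "If the patients need another change in antidepressant monotherapy, they stay in the study protocol, and the changes are annotated". For added treatment: "If the patients need a combination and/or augmentation treatment with antipsychotics and/or mood stabilizers, they are excluded from the study".

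The Blinding section states: "The treating physicians are unblinded". Outcome raters are kept apart from treatment and allocation.

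The Assessments section schedules ratings at "baseline (T0), after 4 (T4), 8 (T8), and 12 (T12) weeks of AD treatment". The primary outcome is percent change in HAMD-17 at week 8.

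Under Statistical analysis, the primary population is fixed thus: "the analyses will be performed for patients who complete the study through week 8". A further analysis is then added: "an intention-to-treat (ITT) analysis will be performed for all the patients who undergo at least one post-treatment assessment for efficacy during the study". The rule for missing scores reads: "The last observation will be carried forward on the HAMD-17".

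**The concern.** Needing combination or augmentation is closely tied to what the trial measures, namely whether the assigned prescribing strategy works. Removing patients for that reason after randomisation means that the patients compared at week 8 are partly selected by outcome. The article does not name who judges the need. The natural reading is the treating physician, who is unblinded.

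The Discussion lists the unblinded clinician as a limitation and offers blinded raters and patients as mitigation. Blinded rating protects the scores that are taken. It does not protect the choice of who is left to be rated.

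The event is foreseeable. Patients enter because current treatment has failed or caused adverse effects, and the Background says that about one third of patients develop treatment-resistant depression. If the arms lose different shares of such patients before week 8, the primary contrast no longer compares the randomised groups.

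**Working it through.** **Step 1. What each removed patient contributes, by time of removal** (plain reading of the two sections together).

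| Removed | Primary model (week 8 completers) | ITT analysis with carried-forward HAMD-17 | Other scales |
|---|---|---|---|
| Before week 4 | Absent | Absent: no post-treatment rating | No post-baseline ratings |
| Weeks 4 to 8 | Absent, with the week 4 score | Present on its face; the pre-augmentation score stands in for week 8 | Week 8 and 12 BDI-II, BAI, MINI-ICF-APP and UKU lost |
| Weeks 8 to 12 | Present | Present | Week 12 ratings lost |

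Carrying forward is named for the HAMD-17 only. Whether exclusion from the study overrides the ITT definition is not stated, so the middle row of the ITT column is open.

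**Step 2. The plan's own figures.** The article gives no expected removal rate. Its sample size is 225 evaluable, inflated for drop-out: 225 / (1 − 0.25) = 300, which reproduces. With a difference of 15 and SD 45, n per arm = 2 × [45 × (z_alpha + z_power) / 15]². This gives 112 per arm with one-sided alpha 0.05, which matches the stated group size, and 142 two-sided, which does not. That mismatch is a separate matter. Here 225 and SD 45 are used only for a standard error.

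**Step 3. Illustration for the primary outcome.** Assumptions, none from the document:
- mean improvement if everyone were kept: m = 30 percentage points in both arms (no true effect);
- share removed before week 8: f;
- mean improvement that the removed patients would have shown: r = 0 or 10 points.

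Completer mean = (m − f × r) / (1 − f). Bias = TGTG completer mean − TAU completer mean (rounded at the end).

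| Removed, TGTG / TAU | r = 0 | r = 10 |
|---|---|---|
| 5% / 5% | 0 | 0 |
| 5% / 10% | 31.58 − 33.33 = −1.75 | 31.05 − 32.22 = −1.17 |
| 5% / 15% | 31.58 − 35.29 = −3.72 | 31.05 − 33.53 = −2.48 |
| 10% / 20% | 33.33 − 37.50 = −4.17 | 32.22 − 35.00 = −2.78 |
| 10% / 5% | +1.75 | +1.17 |

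Negative values count against TGTG. Equal removal with no true effect gives no bias. With a true difference of 15 and 10% removed in each arm (r = 0), the completer estimate is 45/0.9 − 30/0.9 = 16.7.

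**Step 4. Effect on the test.** With 112.5 per arm, the standard error is 45 × √(2/112.5) = 6.0. For a bias b, the two-sided rejection rate under no effect is Φ(b/6 − 1.96) + Φ(−b/6 − 1.96). This is 6.3% for b = 2 and 10.8% for b = 4.2, against a nominal 5%.

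**Step 5. Response rates**, only for an analysis in which removed patients leave the denominator. Assume 35% true response in both arms and that all removed patients are non-responders. With 5% removed in TGTG and 15% in TAU: 0.35/0.95 = 36.8% against 0.35/0.85 = 41.2%, a spurious 4.3 points. With 10% and 20%: 0.35/0.90 = 38.9% against 0.35/0.80 = 43.8%. The sign reverses if the shares do.

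**The case against.** A reader might infer that these patients vanish from every outcome. The document does not support that. On its face, the ITT analysis keeps the HAMD-17 of anyone rated at least once after treatment began. A patient removed after week 4 would then usually count with a poor carried-forward score. A patient removed after week 8 is a full member of the primary analysis. Only removals before week 4 are sure to be missing from both.

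A reader might also infer that the sample size ignores these removals. The Sample size section allows 20–25% drop-out and does not say whether protocol removals are inside that figure, so the inference fails.

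Nor is the different handling of switching and adding a contradiction. A switch stays within the monotherapy strategy under test and an addition departs from it. That is a coherent choice, and it is not challenged here.

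It is also fair to say that the completer restriction is what takes these patients out of the primary estimate. Relabelling them as drop-outs would not bring them back. This shows that the repair needs both parts: continued rating and a wider analysis set. It does not remove the problem.

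Finally, the article condenses a full protocol, which may describe follow-up after removal. The article's wording nonetheless ends participation, and its primary population is stated outright.

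**Conclusion.** The point holds in this form: removal after randomisation, combined with a completer-only primary analysis, drops treatment failures before week 8 from the primary estimate. The ITT analysis is a partial safeguard. It cannot include those removed before week 4, it holds the HAMD-17 at its value before added treatment, and its membership is unresolved. That later ratings stop, and that the prescriber judges the need, are the natural readings but are not spelled out.

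Bias in the primary contrast requires removal to differ between arms or, where there is a true effect, the completer contrast to differ from the as-randomised one. Nothing in the design ensures equal removal, and nothing in the document says which arm would lose more. A reader might infer that the rule works against the test, or for it; neither follows. The shifts of 1.2 to 4.2 points, and the type I error of 6.3% to 10.8% for shifts of 2 to 4.2 points, are illustrations on assumed rates, not estimates for this trial.

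**What to change.** Leave the clinical rule as it is and change what follows from it.

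1. State that starting combination or augmentation ends the study regimen but not participation, and continue the scheduled blinded ratings at weeks 4, 8 and 12.
2. Fit the primary mixed model to all randomised patients with their observed data, in place of week 8 completers. Week 4 scores then contribute even where week 8 is missing.
3. Reconcile the intervention section with the Statistical analysis section, saying explicitly that these patients belong to the ITT set.
4. Report the number and timing of augmentations by arm.
5. Add a sensitivity analysis of response and remission that counts augmented patients as non-responders and non-remitters. It should not be the main analysis, because it would replace a blinded rating with a decision presumably made by an unblinded prescriber.

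The cost is an amendment and a few ratings at visits already scheduled. The statistical downside is that late scores of these patients include the effect of the added treatment, which should be said when the result is interpreted. Recruitment began in February 2020, so ratings not taken for patients already removed cannot be recovered, but any week 4 scores they have can still enter the model.

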### Outcomes

The primary outcome is symptom improvement at week 8, as measured by the percent change in the HAMD-17 score from baseline, between the two groups.

Secondary outcomes include response and remission rates at 4, 8, and 12 weeks according to the HAMD-17.

Tertiary outcomes include (1) changes in scores of depressive symptoms at 4, 8, and 12 weeks compared with baseline according to the BDI-II; (2) response and remission rate at 4, 8, and 12 weeks according to BDI-II; (3) changes in scores of anxiety symptoms at 4, 8, and 12 weeks compared with baseline as measured by the BAI; (4) changes in scores of psychosocial functioning at 8 and 12 weeks compared with baseline as measured by the MINI-ICF-APP; and (5) side effects at 4, 8, and 12 weeks as assessed by the UKU Side Effect Rating Scale.

The response is defined as a ≥50% decrease in the assessment of interest (HAMD-17, BDI-II) at weeks 4, 8, and 12 compared with the baseline. Remission is defined as a score of ≤7 for HAMD-17 and ≤9 for BDI-II.

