### Baseline demographic and clinical features

Age (years) and mean (SD); gender (%F); education (years) and mean (SD); race (%); smokers (%); body mass index (BMI) and mean (SD); age of onset (years) and mean (SD); depression category; moderate, severe, or very severe (%); recurrence (%); presence of psychotic symptoms (%); comorbidity with personality disorders congruent with inclusion/exclusion criteria (%); comorbidity with anxiety disorders (%); presence of psychiatric disorders among the first-degree relatives (%); HAMD-17 at baseline and mean (SD); BDI-II at baseline and mean (SD); BAI-II at baseline and mean (SD); mini-ICF-APP at baseline and mean (SD); MMSE at baseline and mean (SD); UKU at baseline and mean (SD); previous failed adequate treatment; CECA-Q mother antipathy (hostility, coldness) (%); CECA-Q father antipathy (hostility, coldness) (%); CECA-Q mother neglect (%); CECA-Q father neglect (%); CECA-Q physical abuse mother (%); CECA-Q physical abuse father (%); CECA-Q sexual abuse (%); and Paykel score and means (SD).

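### The UKU side-effect outcome is the only scale score not referred to baseline; adjusting for the T0 UKU already collected would add precision, and any incidence analysis needs a new-or-worse rule

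*Protocol article*

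**What the plan says.** All places are in the protocol article.

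- **Outcomes.** The primary outcome is the percent change in HAMD-17 from baseline at week 8. The tertiary list has "changes in scores of depressive symptoms at 4, 8, and 12 weeks compared with baseline according to the BDI-II", "changes in scores of anxiety symptoms at 4, 8, and 12 weeks compared with baseline as measured by the BAI" and "changes in scores of psychosocial functioning at 8 and 12 weeks compared with baseline as measured by the MINI-ICF-APP". Its last item reads "5) side effects at 4, 8, and 12 weeks as assessed by the UKU Side Effect Rating Scale", with no mention of change or of baseline.
- **Assessments.** The UKU is among the scales given at T0 and at weeks 4, 8 and 12.
- **Baseline demographic and clinical features.** The T0 value is to be reported: "UKU at baseline and mean (SD" appears in the list.
- **Eligibility criteria.** Patients are referred "to receive a new AD due to the failure of their current treatment and/or the onset of adverse effects".
- **Aim of the study.** The secondary objective is to "evaluate the use of PGx in decreasing the side effects of antidepressants".
- **Statistical analysis.** For the primary mixed model for repeated measures, "The model includes the fixed effect continuous factor baseline HAMD-17", together with group, visit and their interaction. Response and remission use a generalized linear mixed model, for which no baseline term is named. Tertiary outcomes are exploratory and use the same models.

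**The concern.** A patient who leaves an antidepressant because of adverse effects may still report some of those complaints at week 4 or later. A patient who leaves it for lack of effect may have few. T0 UKU is therefore likely to explain part of the spread in later UKU scores, and that part has nothing to do with the arm.

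The plan collects this information but does not say that the analysis uses it. For the other scales, the outcome definition itself brings in the baseline value. For the UKU neither the definition nor the named covariate does.

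At stake is the sensitivity of the comparison that serves the side-effect objective. The plan also does not say whether the UKU is analysed as a score or as presence of side effects, and the consequence differs between the two.

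**Working it through.** The article gives no UKU mean, standard deviation (SD), event rate or correlation, so it has no figure of its own to reproduce here. The only input taken from it is about 112 patients per group, the evaluable number in the Sample size section (calculated there for HAMD-17). Everything else is assumed and labelled so.

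**1. Text comparison.** Five scales yield a score outcome. Four (HAMD-17, BDI-II, BAI, MINI-ICF-APP) are taken against baseline; the UKU is not.

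**2. UKU as a score, at one visit.** Let r be the correlation between T0 and follow-up UKU (assumed 0.3, 0.5, 0.7), with equal variance at both times. Relative to the raw follow-up score, the variance of the group contrast is:

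- unadjusted change from T0: 2(1 − r)
- follow-up score adjusted for T0 UKU: 1 − r²

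| r | raw score | unadjusted change | adjusted for T0 UKU | reduction by adjusting |
|---|---|---|---|---|
| 0.3 | 1.00 | 1.40 | 0.91 | 9% |
| 0.5 | 1.00 | 1.00 | 0.75 | 25% |
| 0.7 | 1.00 | 0.60 | 0.51 | 49% removed by r² = 0.49, leaving 0.51 |

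The last row needs care: 1 − 0.7² = 0.51 is the variance that remains, so the reduction is 49%; a figure of 51% describes the remainder.

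In SD units, the 95% half-width of the raw contrast with 112 per group is 1.96 × √(2/112) = 0.262. Multiplying by √(1 − r²) gives 0.250, 0.227 and 0.187 for r = 0.3, 0.5 and 0.7.

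**3. Change or raw score, once adjusted.** If Y = a + τ·group + b·T0, then Y − T0 = a + τ·group + (b − 1)·T0. The group effect τ is the same. With T0 UKU in the model, it does not matter which of the two is the outcome.

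**4. UKU as presence of any side effect.** Assume new side effects in 50% of one arm and 35% of the other, and a share q in each arm with a complaint persisting from T0, who count as positive regardless. The observed rate is q + (1 − q)p, so the difference is (1 − q) × 15 points. Power is for a two-sided 0.05 comparison of two proportions with 112 per group.

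| q | observed rates | difference | power |
|---|---|---|---|
| 0 | 50% vs 35% | 15 points | 62% |
| 0.2 | 60% vs 48% | 12 points | 44% |
| 0.4 | 70% vs 61% | 9 points | 29% |
| 0.6 | 80% vs 74% | 6 points | 18.5% |

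**The case against.** The strongest reply has four parts.

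- **The article does not rule out adjustment.** Reusing the same models may well mean that each scale's own baseline replaces HAMD-17. Read literally, the sentence would give BDI-II, BAI and MINI-ICF-APP the HAMD-17 covariate too. The covariate for each exploratory scale is commonly left to an analysis plan, and none is shown. This stands: the matter is unclear, not shown to be wrong. But for the other three scales the outcome definition supports the natural reading, and for the UKU it does not.
- **Randomisation balances T0 UKU in expectation.** This stands. A reader might infer that a chance excess of adverse-effect referrals in one arm biases the result. It does not, and simple randomisation does not change that. At r = 0.5 the part of the contrast carried over from T0 imbalance has a half-width of 0.5 × 0.262 = 0.131 SD. It is already inside the 0.262, since 0.131² + 0.227² ≈ 0.262².
- **Follow-up level is a legitimate outcome.** This stands. The aim of decreasing side effects can be met by comparing the arms after treatment. Redefining the outcome as an unadjusted change would gain nothing at r = 0.5 and would lose precision at r = 0.3.
- **Outcomes other than the UKU also lack a baseline reference.** Remission is an absolute cut-off. It is a threshold state derived from a score, so the statement about scale scores holds.

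A reader might also infer that the plan attributes entry complaints to the study treatment, or that all patients enter because of adverse effects. No section says the first, and the eligibility wording allows failure of treatment, adverse effects or both.

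**Conclusion.** The point holds as a loss of precision and a gap in definition, not as a bias. The UKU is the one scale score with no stated link to its baseline, and the only covariate named for the reused model is HAMD-17.

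For a score analysis, adjusting for T0 UKU would leave 0.91, 0.75 or 0.51 of the residual variance at r = 0.3, 0.5 or 0.7. These correlations are assumed, and the calculation takes one visit, a linear relation and no gain from baseline HAMD-17. For an analysis of presence of side effects, persisting complaints would shrink the difference in proportion to 1 − q. The 50%, 35% and q values are also assumed, with persistence taken as equal in the two arms.

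The outcome is tertiary and exploratory, so no confirmatory conclusion depends on it. It does serve what the Aim section calls the secondary objective, which makes a free improvement worth having.

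**What to change.** Two statements are enough.

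1. In Statistical analysis: the UKU score at weeks 4, 8 and 12 is analysed with T0 UKU as the baseline covariate, in place of or in addition to baseline HAMD-17. Raw score or change may be reported, since the group contrast is then the same.
2. In Outcomes: say whether the UKU is analysed as a score, as incidence or both, and that any item-level or incidence analysis counts only complaints new or worse than at T0.

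The cost is a line in each section, fixed before the data are analysed. T0 UKU is already collected, so no visit, procedure or patient is added.

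### BDI-II remission is any score of 9 or less with no baseline condition, so a patient who starts and stays at or below 9 counts as a remitter without having improved

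*Protocol article*

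**What the plan says.** All references are to the protocol article.

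- **Outcomes**, remission: "Remission is defined as a score of ≤7 for HAMD-17 and ≤9 for BDI-II". No baseline minimum and no required change is attached.
- **Outcomes**, response: "The response is defined as a ≥50% decrease in the assessment of interest (HAMD-17, BDI-II) at weeks 4, 8, and 12 compared with the baseline". This definition, unlike remission, is relative to baseline.
- **Outcomes**, rank: the tertiary outcomes include "response and remission rate at 4, 8, and 12 weeks according to BDI-II".
- **Eligibility criteria**: a current DSM-5 diagnosis of unipolar depression, confirmed by structured interview, "with a Hamilton Depression Rating Scale (HAMD-17) [9] score ≥14". No BDI-II minimum appears among the inclusion or exclusion criteria.
- **Assessments**: "The clinical assessment is carried out at 4 timepoints: baseline (T0), after 4 (T4), 8 (T8), and 12 (T12) weeks of AD treatment". The BDI-II is among the scales used, so a T0 value is available.
- **Statistical analysis**: a generalized linear mixed model is named for response and remission. For the tertiary outcomes, "The analyses of the tertiary outcomes will be performed for exploratory purposes with the same statistical models". No restriction by baseline BDI-II is stated.

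**The concern.** One sentence sets the remission cut-off for both scales, but the entry criteria protect only one of them. On the HAMD-17, nobody can be in remission at entry. On the BDI-II, nothing in the article prevents a patient from starting at or below the cut-off.

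Such a patient cannot move into remission on that scale, yet is counted as having reached it if the score is still 9 or less at the visit. This would raise the BDI-II remission rate in both arms and dilute the difference between them. The response rule has a related weakness at very low baselines: a fall from 4 to 2 is a response, and at a baseline of 0 the percentage decrease has a zero denominator.

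**Working it through.** The article states no figure for BDI-II remission, so there is none to reproduce. The check has two parts.

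**1. What the definitions imply**

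*HAMD-17.* Entry is at 14 or more and remission at 7 or less. Taking the entry score as the baseline score, the smallest possible fall is 14 − 7 = 7 points, and the smallest relative fall is (14 − 7)/14 = 50%. Every HAMD-17 remitter has improved and is also a responder.

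*BDI-II.* With no entry floor, the smallest fall needed for remission is 0 points.

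| BDI-II at T0 → visit | Change | Remission (≤9) | Response (≥50% fall) |
|---|---|---|---|
| 8 → 8 | none | yes | no |
| 8 → 9 | worse by 1 | yes | no |
| 4 → 2 | −50% | yes | yes |
| 0 → any | denominator 0 | depends on the visit score | undefined |

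**2. How much it could matter**

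Inputs, all assumed because the article gives no BDI-II distribution or expected remission rate:

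- p = share of patients with a T0 BDI-II of 9 or less: 2%, 5%, 10%
- s = share of those still at 9 or less at the visit: 90%, equal in both arms
- true remission among the remaining patients: 30% versus 40%

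Observed rate in an arm = (1 − p) × true rate + p × s.

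| p | Lower arm | Higher arm | Difference |
|---|---|---|---|
| 0 | 30.0% | 40.0% | 10.0 points |
| 2% | 0.98 × 0.30 + 0.018 = 31.2% | 0.98 × 0.40 + 0.018 = 41.0% | 9.8 |
| 5% | 0.95 × 0.30 + 0.045 = 33.0% | 0.95 × 0.40 + 0.045 = 42.5% | 9.5 |
| 10% | 0.90 × 0.30 + 0.090 = 36.0% | 0.90 × 0.40 + 0.090 = 45.0% | 9.0 |

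The term p × s is the same in both arms and cancels, so the difference is (1 − p) × 10 points whatever the value of s.

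*Other assumed rates.* Take 25% versus 40%, s = 100%, and 112 patients per group (the approximate group size in the Sample size section). Power is for a two-sided 5% comparison of two proportions.

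| p | Observed rates | Difference | Power, rule as written | Power, baseline ≥10 only |
|---|---|---|---|---|
| 0 | 25.0% vs 40.0% | 15.0 points | 0.671 | 0.671 |
| 2% | 26.5% vs 41.2% | 14.7 | 0.644 | 0.662 |
| 5% | 28.75% vs 43.0% | 14.25 | 0.605 | 0.648 |
| 10% | 32.5% vs 46.0% | 13.5 | 0.544 | 0.625 |

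The restricted analysis has fewer patients, 112 × (1 − p) per group, but keeps the full 15-point difference. At each p above zero it has more power than the rule as written.

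**The case against.** **Few such patients may exist.** Everyone enrolled has an interview-confirmed current depressive diagnosis, a HAMD-17 of at least 14, and a referral for a new antidepressant. The severity categories listed under Baseline demographic and clinical features start at moderate. Nothing shows that low BDI-II scorers will be enrolled in any number. This stands: p is an assumption and is probably small.

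**The dilution is small against sampling error.** With 30% versus 40% and 112 per group, the standard error of the difference is √(0.21/112 + 0.24/112) = 6.3 points. A loss of 0.2 to 1.0 points is about 3% to 16% of that. This also stands.

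**Remission is a state and response is a change.** Defining them separately is coherent, and a patient going from 8 to 9 is a non-responder who shows as worse in the continuous analysis. That is a fair defence of an absolute cut-off. It does not defend counting a patient who was never above the cut-off on that scale as having remitted.

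**It may be settled elsewhere.** The evaluable set for an exploratory binary outcome is often left to the analysis plan, which is not shown. But the article states the remission rule in full, and an analysis plan that restricted it would be changing the published definition.

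**Stronger readings that the article does not support.**

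- A reader might infer that a low T0 score alone makes a patient a remitter. The score must still be 9 or less at week 4, 8 or 12.
- A reader might infer that entry rests on the HAMD-17 alone. It is the only severity threshold, but the diagnosis is also required.
- A reader might infer that a planned comparison of BDI-II with HAMD-17 rates is spoiled. No such comparison is planned.

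**Conclusion.** The point holds as a minor flaw in a stated definition. As written, BDI-II remission includes patients who did not improve or who worsened, and BDI-II response is undefined at a baseline of 0.

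Under the assumptions above (2% to 10% starting at 9 or less, 90% of them staying there, true rates 30% versus 40%), the rates rise by 1.2 to 6.0 points in the lower arm and 1.0 to 5.0 points in the higher arm. The difference falls from 10 points to between 9.8 and 9.0.

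It would be wrong to infer that the rule favours one arm. Randomisation balances low scorers in expectation, so the expected effect is dilution, provided the chance of staying low is the same in both arms. The primary outcome and the HAMD-17 response and remission outcomes are unaffected. Only the tertiary, exploratory binary BDI-II outcomes are touched.

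**What to change.** In the Outcomes section, state that BDI-II response and remission are evaluated among patients with a BDI-II score of 10 or more at T0, and that all patients stay in the analysis of BDI-II change. It would help to report the number excluded in each arm.

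The T0 score is already collected. It precedes the new treatment and comes from blinded patients, so restricting on it keeps the comparison a randomised one. The rule also removes the undefined response at a baseline of 0. It does not make every BDI-II remitter a responder: a fall from 15 to 9 is 6/15 = 40%. It only ensures that remission means crossing the cut-off.

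The cost is one sentence and a slightly smaller denominator for the two binary BDI-II outcomes. Making the change before the data are analysed avoids a post hoc choice of denominator.
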